## 4.8 Primary and secondary endpoints

### Primary endpoint

The primary endpoint of this clinical investigation is the **feasibility** of the methods and of a full-scale randomised controlled trial. This will be assessed by the recruitment rate, retention rate and adherence rate, a structured adverse events log, a Smiley Likert Scale asking four predefined questions on the acceptance of the intervention, as well as a semi-structured observation during the RAGT intervention for understanding the intervention context and process.

### Recruitment, retention and adherence rates

The feasibility of the methods and of conducting a larger trial will be explored using predefined criteria, recording monthly recruitment and adherence rates to the RAGT intervention. Using a structured log, adherence to the RAGT will be recorded, including reasons (e.g., discontinuation due to lack of interest or injury). Any non-retention will also be recorded with reasons (e.g., consent withdrawn). ***This evaluation will not involve any***

***additional measures for the patients.***

The criteria for feasibility success will be:

- a) a target recruitment rate 3 patients per month.,
- b) a target retention rate of 85%,
- c) a target minimum adherence rate of 75% to the RAGT interventions (12 sessions out of a maximum of 16)

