## **5 PARTICIPANTS**

### **5.1. Sampling and participant recruitment**

Stratified sampling will be used in this clinical investigation, with eight strata representing the different neurological diseases, as well as patients post stroke in the subacute and chronic phases who are severely and mild to moderately affected, respectively. This strategy will be chosen based on the primarily quantitative nature of this study.

All patients with a first-ever ischemic or hemorrhagic stroke, multiple sclerosis (MS), Parkinson's Disease (PD), a spastic para- or tetraplegia caused by any type of spinal cord lesion, mild to medium grade hereditary ataxia, acute or chronic inflammatory demyelinating polyneuropathy (e.g., GBS, CIDP) or a motoneuron disease (e.g., ALS) treated at the Reha Zentrum Münster during the recruitment period will be checked by the medical staff with regard to their suitability for participation in the clinical investigation. All patients who meet the inclusion criteria of this study and do not meet any of the exclusion criteria will be informed verbally and in writing about the study by the PI or investigator. After determining the general eligibility (inclusion criteria) and the consent of the patient i.e., their interest in participating in the study, a screening will be carried out. Using predefined criteria for intact cognitive functioning, with a cut-off score  $\geq 24/30$  points on the Mini Mental State Examination (MMSE) (Folstein et al., 1975), patients with moderate to severe cognitive impairment will be excluded. Furthermore, patients without walking impairment as defined by a neurological exam and an FAC score of 5 will be excluded. In the absence of these exclusion criteria, the study inclusion described below will take place.

After having provided the patient with the patient information sheet, an appropriate period of reflection for the patient, the opportunity for queries and answers and the patient's consent to participate, the informed consent form will then be dated and signed by both the patient and the doctor. The investigator will note the participation on a specific patient identification list. It will be used to later identify the patient and contain the identification number (ID), the full name of the patient, the date of birth and the date of admission to the clinical investigation. The patient identification list will remain at the trial centre after the clinical investigation has been completed.

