### 5.3 Sample size

This clinical investigation will be a prospective comparative multiple case study. A comparative multiple case study design with mainly quantitative data but also qualitative data analyses and a cross-case analysis will be used. Mixing methods is a form of triangulation in research seen as mitigating the weaknesses found in single methods (Heale & Forbes, 2013). Triangulation in research is the use of more than one approach to researching a question. The objective is to increase confidence in the findings through the confirmation of a proposition using two or more independent measures (Noble & Heale, 2019). The combination of findings from two or more rigorous approaches provides a more comprehensive picture of the results than either approach could do alone (Noble & Heale, 2019). A multiple case-oriented research strategy will be adopted to acquire knowledge about the outcomes from RAGT within the 8 different patient (disease) groups, learn about similarities and differences between individual cases and neurological disorders within study intervention periods and emerging patterns (Ababacar et al., 2020; Nordbeck, 2013).

The primary outcome of this study will be the feasibility of the methods and of a larger randomised controlled trial. Based on the study design (Yin, 2014) and primary outcome, no formal sample size calculation has been carried out. Based on the different prevalence rates of the diseases investigated in this clinical investigation, 5 patients with severe stroke in the subacute phase will be included in this study, 5 patients with mild to moderate stroke in the chronic stage, 5 patients with MS, 5 patients with PD, 2 patients with spastic para- or tetraplegia caused by any type of spinal cord lesion, 2 patients with mild to medium grade hereditary ataxia, 2 patients with acute or chronic inflammatory demyelinating polyneuropathy (e.g., GBS, CIDP) and 2 patients with motoneuron disease (e.g., ALS), resulting in a total sample size of 28. Based on the study design, methods and objectives, no further patients will be included to account for attrition, which is expected at 10%.

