### Study-specific:

Recruitment duration: 15 months

1.2.2022 Planned start: First Patient First Visit (FPFV)

31.3.2023, 2022 Last Patient First Visit (LPFV)/Last Subject In (LSI)

30.4.2023 Planned end: Last Patient Last Visit (LPLV)/Last Subject Out (LSO)

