## **7.6 Early termination or suspension of the clinical investigation**

The sponsor is authorised to terminate the study early or to suspend the study because of relevant medical or administrative causes. The criteria and reasons for ending the study are documented in detail. Patients who were still receiving treatment at the time of the termination of the trial will be asked to undergo a final examination as part of post-intervention testing at the next possible opportunity. The results of these tests will be documented in the CRF. Should an investigator have ethical concerns regarding the continuation of the study, these must be communicated to the sponsor immediately.

The sponsor is authorised to end the clinical trial prematurely if

- There is unequivocal evidence of treatment benefit or harm
- The patient recruitment rate cannot be reached,
- Serious, unresolvable problems arise with the quality of the data collected,
- Unforeseeable circumstances arise in the trial site, which means that the continuation of the clinical investigation is not permissible,
- Unexpected unacceptable side effects occur from the RAGT intervention,
- Unreasonable risks arise (decision after another risk/benefit assessment),
- New scientific knowledge acquired during the study no longer permits the continuation of the study (e.g., reports of unsuspected and unacceptable treatment side effects),
- No trends emerge as for the benefit of the RAGT intervention after a reasonable number of patients have been investigated and the results clinically interpreted,
- There is a lack of compliance in a large number of patients,
- Withdrawal of the LEXO® robotic gait trainer from the market

The PI can decide whether to terminate the study in consultation with the sponsor.

Should an investigator have ethical concerns regarding the continuation of the study, these must be communicated to the sponsor immediately.

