## 8.2. Planned statistical analysis

IBM SPSS Software, release 27.0 (IBM Corporation, Armonk, NY, USA) and GraphPad Prism 9, San Diego, California, will be used for the data analyses. Statistical significance will be defined as a two-tailed p-value  $<0.05$ . The percentage of missing data will be recorded. Using Little's test of missing completely at random (MCAR) (Little, 1988) the data will be checked, signified by a p-value  $>0.05$ .

Descriptive statistics will be used for the baseline demographic variables, primary and secondary endpoints. Continuous data will be checked for normal distribution using the Shapiro Wilk Test, Q-Q plots and histograms. Raw count (absolute and relative frequencies, N (%)) will be presented for count data (N females and males, N falls, most affected body part, and N adverse events if any, adherence (N of training sessions), recruitment, retention and adherence rates) and nominal data (gender)). Medians (range; 25th and 75th percentiles) will be reported for ordinal data (MMSE, NIHSS, EDSS, UPDRS, H&Y, ASIA Scale, SARA, MAS, ONLS, ALSFRS-R, FAC, TCT, FES-I, EQ-5D-5L, BDI-II, FSS, GAS, Smiley Likert Scale), mean (standard deviation (SD)) will be reported for continuous data (age, years of education, disease duration, 10MWT, FGA, 6MWT, TUG, FSST and MFRT).

With respect to the primary endpoint of feasibility, the recruitment rate (%) will be estimated by dividing the number of consenting patients by the N of eligible patients, multiplied by 100. The retention rate determined by dividing the N of patients who completed the study by the N of the total sample, times 100. Adherence rates will be calculated by dividing the N of RAGT sessions (16x) performed by the patients, divided by the N of the scheduled RAGT training sessions over the 4 week study period, times 100 (Osterberg & Blaschke, 2005). The eligibility, recruitment and adherence rates will be calculated with their 95% CI according to the Wilson 'score' method cited by Newcombe (Newcombe, 1998); when the proportion is close to 0 or 1, a Poisson approximation as described by Brown and colleagues will be used (Brown et al., 2001). Furthermore, the number of (serious) adverse events and side effects will be reported.

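### Feasibility criterion (a), 3 patients per month, is missed by a trial that recruits exactly on the protocol's own schedule (2.0 per month), and section 8.2 gives the name recruitment rate to a different quantity that has no threshold

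*Protocol*

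**What the plan says.** Section 4.8 (Recruitment, retention and adherence rates) introduces three numerical thresholds with "The criteria for feasibility success will be". The first is "a target recruitment rate 3 patients per month"; the other two concern retention and adherence. The same subsection says that monthly recruitment will be recorded.

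Section 5.3 sums eight strata, "resulting in a total sample size of 28", and adds that "no further patients will be included to account for attrition, which is expected at 10" per cent. Section 7.5 rules out replacing patients who leave. Enrolment is therefore capped at 28.

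Section 5.6, like the synopsis, gives "Recruitment duration: 15 months". It dates first patient first visit at 1.2.2022, last patient first visit at 31.3.2023 (a line that also carries a stray 2022) and last patient last visit at 30.4.2023.

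Section 8.2, again repeated in the synopsis, states for the primary endpoint that "the recruitment rate (%) will be estimated by dividing the number of consenting patients by the N of eligible patients, multiplied by 100", with a Wilson 95% interval. Section 7.6 lists among the sponsor's grounds for ending the study early: "The patient recruitment rate cannot be reached". It gives no figure and no definition there.

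**The concern.** Recruitment is one of only three feasibility components with a number attached, and the results are meant to inform a full-scale randomised trial. Two things do not fit together.

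First, the threshold is half as high again as the rate that the protocol itself schedules. Meeting the timetable to the day means missing the criterion, and nothing in the protocol explains why a pace faster than planned should be the mark of success.

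Second, one term carries two meanings. Section 4.8 means patients per calendar month; section 8.2 means the share of eligible patients who consent. The first has a threshold but no calculation in the analysis section. The second has a calculation and an interval but no threshold. Unless this is settled before results are known, a good consent percentage could be reported under the heading of recruitment rate although fewer than 3 patients per month were enrolled, and a reader could not tell which figure the protocol meant.

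**Working it through.** **Inputs.** Target 3 per month (4.8). Strata 5, 5, 5, 5, 2, 2, 2, 2 (5.3). No inflation (5.3) and no replacement (7.5). Dates and labelled duration (5.6).

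**Sample size, reproduced.** 5+5+5+5+2+2+2+2 = 28, as stated.

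**Length of recruitment.**
- First patient first visit to last patient first visit, 1.2.2022 to 31.3.2023: 424 days inclusive; 424/30.44 = 13.9, that is 14 calendar months.
- First patient first visit to last patient last visit, 1.2.2022 to 30.4.2023: 454 days inclusive; 454/30.44 = 14.9, that is 15 calendar months.

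The labelled 15 months thus matches first patient in to last patient out, not the period in which patients are enrolled.

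**Rate implied by the schedule (patients / months).**

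| Period used | Implied rate | Share of the target of 3 |
|---|---|---|
| 14 months (dates) | 28/14 = 2.00 per month | 2.00/3 = 67% |
| 15 months (label) | 28/15 = 1.87 per month | 1.87/3 = 62% |

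**What the target requires.** With enrolment fixed at 28, an average of 3 per month means that the 28th patient is enrolled within 28/3 = 9.33 months. That is 14 − 9.33 = 4.7 months before the planned last-patient-in date, or 15 − 9.33 = 5.7 months before the end of the labelled period.

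**How likely that is if recruitment runs at the scheduled pace.** The count is fixed and the time varies, so the question is whether the 28th arrival falls within 9.33 months. Assume Poisson arrivals at a true rate of 2 per month. The time to the 28th arrival is then gamma with shape 28 and rate 2, and P(time ≤ 9.33) = P(Poisson with mean 2 × 9.33 = 18.67 is at least 28) = 0.026, about 2.6%.

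**The two definitions side by side.**

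| | Section 4.8 | Section 8.2 |
|---|---|---|
| Quantity | patients per month | consenting / eligible × 100 |
| Threshold | 3 per month | none |
| Calculation and interval | none defined | defined, Wilson 95% |

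The percentage cannot be converted into the monthly rate without the number of eligible patients seen per month, which the protocol does not give. Neither figure can stand in for the other.

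**The case against.** The best defence is that target and timetable do different jobs. The dates may be an outer planning window and 3 per month a goal; faster recruitment would satisfy both, so they do not exclude each other. That is correct, and the criterion is attainable. But section 4.8 lists the figure as a success criterion, not as an aspiration, and no text presents the dates as a generous upper limit.

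It can also be said that the data for criterion (a) will exist: section 4.8 records monthly recruitment, section 8.2 lists recruitment among the items to be presented as raw counts, and an interval or a detailed formula may properly be left to a statistical analysis plan that is not at hand. This stands in part. The information will not be lost. What remains is that the protocol's own analysis section attaches the name to another measure.

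The 14-month figure rests on a date line with a visible slip. The labelled 15 months gives a still lower rate, so the conclusion does not depend on it.

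Four stronger readings may tempt a reader and are not supported:
- That a trial on schedule would be declared infeasible. Section 4.8 says that feasibility will be explored against the criteria and gives no rule that one missed target decides the matter. Adverse events, acceptability and observation also count.
- That section 7.6 entitles the sponsor to stop a trial running on schedule. The clause gives no figure and no link to criterion (a); this is one reading of undefined wording.
- That 42 patients (3 × 14) would be needed, with a probability or confidence interval built on that count. Enrolment stops at 28, so 42 cannot occur, and a planned number has no sampling error.
- That the consent percentage is biased because section 5.1 seeks "the consent of the patient i.e., their interest in participating in the study, a screening will be carried out" afterwards, or because strata fill up. Nothing says that decliners are left out or how patients are counted once a stratum is full; such counting rules are ordinary analysis-plan detail.

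**Conclusion.** The point holds in two parts. Criterion (a) conflicts with the schedule: recruitment exactly as planned gives 2.0 per month on the dates, or 1.87 on the labelled duration, against 3. Meeting it requires enrolment to finish in 9.3 months. The 2.6% chance of that assumes Poisson arrivals at a constant true rate of 2 per month and ignores the stratum quotas; it only illustrates the size of the gap, and the finding does not depend on it. Separately, section 8.2 uses the term recruitment rate for a proportion without a threshold and leaves undefined the rate on which criterion (a) is judged.

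This is a misalignment between a target, a timetable and an analysis definition. It does not show that the trial must fail or could be stopped for keeping to its plan. It deserves correction because it concerns a numerical success criterion of the primary endpoint, and the correction should come before the recruitment results are known.

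**What to change.** 1. In section 8.2 and the synopsis, define the recruitment rate as patients enrolled divided by months open to recruitment, counted to the last enrolment, and state that criterion (a) is judged on it. Rename the percentage of eligible patients who consent the consent rate.
2. Make target and schedule agree. Either restate the target at about 2 per month (28 in 14 months), or keep 3 per month and set the last-subject-in date at about 9 to 10 months after the start. The choice should follow from the rate that the follow-up randomised trial needs; lowering the target merely to fit the timetable would turn criterion (a) into a check of the timetable.
3. In section 5.6 and the synopsis, correct the recruitment duration to 14 months, or to the new period if the date moves, and remove the stray year.
4. In section 7.6, say which recruitment rate is meant.

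The cost is wording in 4.8, 5.6, 7.6, 8.2 and the synopsis. No patients or procedures are added. The stated target may become less ambitious, or the planned recruitment period shorter.

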**Adverse events**

Any adverse events and side effects will be systematically recorded and evaluated using a formal log including the type of adverse event, dates, severity, causality differentiated into serious/non-serious, actions to restore or improve the patient's wellbeing and outcome of the event. Study related adverse events such as training-related injuries will be treated and paid for. Severe adverse events will lead to early clinical investigation termination. ***This monitoring will be performed throughout the study.***

**Acceptability of the intervention**

Acceptability of the intervention will be assessed using a Smiley Likert Scale asking four predefined questions on the acceptance of the intervention (please see CRF), as well as a semi-structured observation during the RAGT intervention for understanding the intervention context and process, recognising patterns, and moving beyond selected outcome measures. This is of clinical relevance because high acceptability may help increase motivation and adherence in patients. ***The Likert scale will be used as part of the clinical investigation (2-4 min).***

**Secondary endpoints**

The secondary endpoints for this clinical investigation and how they will be assessed are presented in Table 7. The validated German version of all assessments will be used, which have demonstrated good to excellent properties. In addition, the collection timepoints are shown. The assessments which will be ***performed in clinical routine are highlighted in green***, with the remaining assessments being ***performed as part of the clinical investigation (highlighted yellow)***.

**Table 7:** Secondary endpoints and assessment

| No. | Secondary endpoint | Assessment                                                   | Scr | BL  | PI | IV |
|-----|--------------------|--------------------------------------------------------------|-----|-----|----|----|
| 1.1 | Number of falls    | Falls log [ambulatory patients] (see CRF)                    |     | x   | x  |    |
| 1.2 | Walking ability    | Functional Ambulation Categories (FAC) [ambulatory patients] | x   | (c) | x  |    |

|      |                                                                                                           |                                                                                       |    |   |    |   |
|------|-----------------------------------------------------------------------------------------------------------|---------------------------------------------------------------------------------------|----|---|----|---|
| 1.3  | Walking speed                                                                                             | 10-Metre Walk Test (10MWT)
[ambulatory patients, assessed in clinical routine]     |    | x | x  |   |
| 1.4  | Dynamic balance during walking                                                                            | Functional Gait Assessment (FGA)
[ambulatory patients]                             |    | x | x  |   |
| 1.5  | Walking distance                                                                                          | 6-Minute Walk Test (6MWT)
[ambulatory patients, assessed in clinical routine]      |    | x | x  |   |
| 1.6  | Functional mobility                                                                                       | Timed Up and Go test (TUG)
[ambulatory patients]                                   |    | x | x  |   |
| 1.7  | Dynamic balance                                                                                           | Four-Square Step Test (FSST)
[ambulatory patients]                                 |    | x | x  |   |
| 1.8  | Trunk movement                                                                                            | Trunk Control Test (TCT) [non-ambulatory patients]                                    |    | x | x  |   |
| 1.9  | Limits of stability with respect to trunk movements                                                       | Modified Functional Reach Test (MFRT) [non-ambulatory patients]                       |    | x | x  |   |
| 1.10 | Fall-related self-efficacy                                                                                | Falls Efficacy Scale- International Version (FES-I)                                   |    | x | x  |   |
| 1.11 | Health-related quality of life                                                                            | 5-level EQ-5D version (EQ-5D-5L)                                                      |    | x | x  |   |
| 1.12 | Depression                                                                                                | Beck Depression Inventory, second edition (BDI-II)                                    |    | x | x  |   |
| 1.13 | Fatigue                                                                                                   | Fatigue Severity Scale (FSS)                                                          |    |   | x  |   |
| 1.14 | Goal definition and evaluation of its achievement                                                         | SMART defined movement-related individual goal (a); Goal Attainment Scaling (GAS) (b) | ax |   | bx |   |
| 1.15 | Gait parameters (gait speed, walking distance, number of steps and step length)                           | Measured by LEXO® during the intervention as part of the clinical routine             |    |   |    | x |
| 1.16 | Body weight and gait support (percentage of body weight support, percentage of active/passive gait modes) | Measured by LEXO® during the intervention as part of the clinical routine             |    |   |    | x |

Abbreviation: Scr=screening; SMART=specific, measurable, attractive, realistic and terminated; c=data carryover to baseline if patient has passed the screening; BL=baseline; PI=post-intervention; IV=intervention period (at all intervention sessions)

